## **Protocol Title: Evaluating Trikafta for the treatment of patients with non-cystic fibrosis bronchiectasis (NCFBE)**

---

A participant will be considered lost to follow-up if he or she fails to return for any scheduled visit and is unable to be contacted by the 'main' study site staff.

The following actions will be taken if a participant fails to return to the clinic for a required 'main' study visit:

- The study investigators will attempt to contact the participant and reschedule the missed visit within 2-5 days, and counsel the participant on the importance of maintaining the assigned visit schedule and ascertain if the participant wishes to and/or should continue in the 'main' study.
- Before a participant is deemed lost to follow-up, the investigator or designee will make every effort to regain contact with the participant (where possible, 3 telephone calls and, if necessary, a certified letter to the participant's last known mailing address or local equivalent methods). These contact attempts should be documented in the participant's medical record or study file.
- Should the participant continue to be unreachable, he or she will be considered to have withdrawn from the 'main' study with a primary reason of lost to follow-up.

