The study will examine iPSC-derived airway epithelial monolayers (an *in vitro* analytic tool) as a predictive means for identifying individuals with NCFBE most likely to show respiratory benefit from Trikafta™. As part of the protocol, we will perform an open-label clinical trial of orally-administered Trikafta™ in subjects with NCFBE. Subjects will be given the Study Drug elexacaftor 100 mg/tezacaftor 50 mg/ivacaftor 75 mg (2 pills once daily in the morning) and ivacaftor (150 mg) once daily in the evening, as the FDA-registered agent, Trikafta™. Dose and schedule will be identical to what has already been FDA-approved for effective treatment of CF. Trikafta™ is not approved for use in NCFBE. Enrollment is planned at Emory University. Patients enrolled in the trial will have one disease-causing CFTR variant and/or modestly elevated sweat chloride values (30-60 mEq/L), but without clinical findings sufficient for a diagnosis of cystic fibrosis.

Human subject participation in the ‘main’ study will consist of a screening day (-28), day 1 (+/- 2), day 7 (+/- 2) [phone call visit], day 14(+/-2), day 28 (+1/- 2) and day 56 (+/-2) follow up (wash-out). The visits will include patient history with concomitant medication review, physical exam, safety laboratory assessments (renal and liver panels, CBC/Diff, urinalysis), serum and urine pregnancy testing, CFTR genotype, spirometry, O2 saturation, sweat chloride test, cutaneous punch biopsy for iPSC derivation, EKG, drug accountability and questionnaire (QOL assessment), concomitant medication review, and adverse event assessment. No longer-term follow-up beyond day 56 is being planned (except for possible cutaneous biopsy by day 70 if needed (see below).

We anticipate the screening and enrollment visit will require 4-6 hours to complete the informed consent, medical history, O2 saturation, concomitant medication review, physical exam, safety laboratory assessments (CBC/Diff, RENAL/LFT chemistry panel, and urinalysis),

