**Protocol Title: Evaluating Trikafta for the treatment of patients with non-cystic fibrosis bronchiectasis (NCFBE)**

---

EKG, CFTR genotyping, questionnaire, serum pregnancy test for females, sweat chloride test, and spirometry.

On day 1 (when subject returns), the visit will require approximately 6 hours to complete the concomitant medication review, adverse event assessment, interval medical history, physical exam, O2 saturation, safety laboratory assessments (CBC/Diff, RENAL/LFT chemistry panel, and urinalysis), questionnaire, sweat chloride, urine pregnancy test for females, spirometry, cutaneous punch biopsy (3mm), drug dispensing, and drug administration. The cutaneous punch biopsy may occur at any time between the Screening Visit and Day 1 based on dermatology clinic schedule availability.

- 1 Cutaneous 3 mm punch biopsy (performed here (and on day 56 (or up to two weeks later) if necessary to produce additional iPS cells)): In this procedure, a circular blade is rotated from epidermis to subcutaneous fat, yielding a ~ 3 mm cylindrical core of tissue. Extending the skin perpendicular to the incision line allows for facile closure, which can typically be accomplished with a single suture. Pain is well-managed by local subcutaneous anesthetic. A small fibrotic scar can be minimized by linear closure of the biopsy. Significant pain, bleeding, or infection are very rare.

The subject will complete a phone call visit on day 7 (+/-2) that will require approximately 30 minutes to complete concomitant medication review, interval medical history, and adverse event assessment.

On day 14 (+/-2) the subject will return for a visit that will require approximately 4-6 hours to complete concomitant medication review, interval medical history, adverse event assessment, physical exam, drug dispensing and drug return, questionnaire, safety laboratory assessments (CBC/Diff, RENAL/LFT chemistry panel, and urinalysis), sweat chloride test, EKG, O2 saturation and spirometry.

On day 28 (+1/-2) we will conduct interval medical history, adverse event assessment, concomitant medications, physical exam, sweat chloride test, spirometry, O2 saturation, safety laboratory assessments (CBC/Diff, RENAL/LFT chemistry panel, and urinalysis), questionnaire, and drug return. This visit should require 4-6 hours to complete. This visit should occur no later than Day 29 since a 28-day supply of Trikafta™ will be provided.

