### **7. Statistical Analysis Plan**

Goals of the 'main' study are to determine the clinical response to Trikafta™ and whether *in vitro* responsiveness of iPS cell-derived airway monolayers predict Trikafta™ effectiveness. Primary outcomes comprise the ability of iPSC-derived monolayers to predict respiratory benefit from Trikafta™ after 4 weeks of *in vivo* treatment. Primary analysis will include an estimate of clinical response rate of Trikafta™ at week 4 of treatment and a 95% confidence interval using the exact method proposed by Blaker (Blaker, 2000). A responder is defined as any subject with an improvement, from baseline, in  $FEV_1 > 5\%$  predicted.  $FEV_1$  will also be considered continuously. A two-sided 0.05 alpha level paired t-test comparing the baseline and week 4  $FEV_1$  measurements, along with the test and 95% associated confidence interval, will be evaluated.

In this study, if at least 15% of subjects meet the definition of responder, we will view this as initial evidence of a favorable result. Overall response rate will be accompanied by an exact 95% confidence interval. To determine the role of iPS *in-vitro* response to Trikafta™, we will compare the  $\Delta$  Isc (change in Isc) among Trikafta™ responders and Trikafta™ non-responders using an ANCOVA test. Additionally, we will correlate the  $\Delta$  Isc obtained from *in vitro* experiments with the change in FEV1% predicted (post minus pre) using Spearman's rank-order correlation with an associated 95% confidence interval. We will also test whether the iPS response reaches a CFTR functional threshold of 30% wild-type levels (a magnitude of activity in primary airway epithelial cells viewed as potentially relevant to clinical benefit). In a sensitivity analysis, we will replicate the FEV1 analysis with sweat chloride responses and determine the *in vivo* response rate.

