**Sample size**

We will test the null hypothesis that the true Trikafta™ response rate of NCFBE individuals is  $\leq 1\%$  vs. the alternative hypothesis that the true Trikafta™ response rate is  $\geq 15\%$ . We will initially enroll 16 subjects. If none of these subjects exhibit a clinical response (defined as  $> 5\%$  improvement of % predicted FEV1 from baseline), the study may be considered for termination. Otherwise, we intend to enroll a total sample size of 29 individuals (or 30 subjects, in the unlikely event that an individual discontinues participation; i.e., subjects who do not complete the study will be replaced). In this design, if Trikafta™ is ineffective, the probability of early termination after 16 subjects is 85% and only a 2.8% chance of concluding the drug is effective (type I error). If Trikafta™ is effective, there is a 90.04% chance of reaching this conclusion. If fewer than 2 patients (of 29 patients total) of the overall cohort show a clinical effect, Trikafta™ will be considered ineffective. To demonstrate the ability of iPS cells to predict clinical benefit, 16 (29) patients will provide at least 80% power to detect a significant Spearman correlation of at least  $r = 0.8$  (.53) between the changes in clinical outcomes with changes in short circuit current as measured in iPS cells. Tabular details of this analysis are provided below. Power calculations were performed using PASS v. 14 (Kaysville, UT) with a two-sided Z-test and a significance level of 0.05.

|                            | Cumulative # of responses | Decision                                                                                                             | 95% Confidence Interval (CI) |
|----------------------------|---------------------------|----------------------------------------------------------------------------------------------------------------------|------------------------------|
| Stage 1: Enter 16 subjects | 0                         | Consider Termination of the trial because the agent is ineffective.
Response rate is <math>\leq 1\%</math> | LB of 95% CI is $< 1\%$      |
|                            | At least 1                | Inconclusive result, continue                                                                                        | 95% CI contains 1%           |

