Once the four-week treatment period is complete, participants will no longer receive Trikafta™. There is a chance that the NCFBE will improve when taking Trikafta™. However, NCFBE symptoms may appear to worsen after the participant stops taking Trikafta™ as respiratory function returns to baseline.

Women:

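### The schedule table lets the primary week-4 visit fall on Day 30, past the text's Day 29 limit and after the 28-day drug supply has run out

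*Protocol*

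**What the plan says.** **Schedule table (Section 6, Procedures Involved).** The column heading for Study Visit 4 is Day 28 plus or minus 2 days, and it is repeated where the table continues. Spirometry is marked in that column.

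**Text of Section 6.** The participation summary gives "day 28 (+1/- 2) and day 56 (+/-2) follow up (wash-out", and the Day 28 paragraph repeats +1/-2. That paragraph adds the reason: "This visit should occur no later than Day 29 since a 28-day supply of Trikafta™ will be provided". Dosing starts at the Day 1 visit.

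**Section 7.** The primary analysis is an "estimate of clinical response rate of Trikafta™ at week 4 of treatment". A responder is a subject whose FEV1 rises from baseline by more than 5% predicted. All subjects are analysed, however long they took drug. Under the Sample size heading, the final rule is that the drug is considered ineffective "If fewer than 2 patients (of 29 patients total) of the overall cohort show a clinical effect". Stage 1 asks whether any of the first 16 subjects responds.

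**Section 15, Withdrawal of Participants.** The steps apply "if a participant fails to return to the clinic for a required 'main' study visit". Staff are to attempt to contact the participant and "reschedule the missed visit within 2-5 days". The bullet also tells them to counsel the participant on keeping to the visit schedule. It mentions neither windows nor drug supply.

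**Section 16, Risk to Participants.** Symptoms may seem worse after drug stops "as respiratory function returns to baseline". No time course is given.

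**The concern.** The text shortens the late side of the Day 28 window to one day for a stated reason: the drug runs out. The table does not carry that limit. Site staff commonly book from the schedule table, and a Day 30 visit booked that way looks compliant although the participant has no drug left.

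The quantity at stake is the primary one. Response is defined at week 4 of treatment, and the protocol itself expects lung function to fall back once drug stops. An FEV1 taken after the last dose could understate the on-treatment change and turn a responder into a non-responder. The decisions turn on single subjects: 0 against 1 of 16 at stage 1, and 1 against 2 of 29 at the end. Because the analysis includes everyone regardless of exposure, nothing in the protocol removes or flags such a value.

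The rebooking instruction in Section 15 is a second, weaker route to the same result, because it covers every required visit and sets no cap for Day 28.

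**Working it through.** **Inputs.** First dose on Day 1, 28-day supply, Day 29 limit and +1/-2 window (Section 6 text); plus or minus 2 window (Section 6 table); rebooking interval of 2 to 5 days (Section 15). Assumption: no missed doses, so no leftover tablets.

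**1. The plan's own limit.** Last supplied dosing day = 1 + 28 - 1 = Day 28. The first day without drug is Day 29, which is the +1 limit. A Day 29 visit has no full drug-free day before it. The text is consistent with the supply.

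**2. Table against text.**

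| Source | Window | Last day allowed | Days after last dose (d - 28) | Full drug-free days before visit (d - 29) |
|---|---|---|---|---|
| Text | 28 - 2 to 28 + 1 = Day 26 to 29 | 29 | 1 | 0 |
| Table | 28 - 2 to 28 + 2 = Day 26 to 30 | 30 | 2 | 1 |

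The two differ by exactly one day, Day 30.

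**3. Rebooking instruction.** If the new date is the missed day plus 2 to 5:

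| Visit missed on | New date | Dates within the Day 29 limit |
|---|---|---|
| Day 26 | Day 28 to 31 | Day 28, 29 |
| Day 27 | Day 29 to 32 | Day 29 |
| Day 28 | Day 30 to 33 | none |

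For a visit missed on Day 28, these dates are 2 to 5 days after the last dose. If the interval is instead an outer limit, Day 29 (one day later) satisfies both instructions.

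**4. Sensitivity to the start day.** Section 6 allows Day 1 plus or minus 2. If visit days are counted from a nominal Day 1 while dosing starts on nominal day -1, 1 or 3, the last supplied dose falls on nominal day 26, 28 or 30. A Day 30 visit is then 4, 2 or 0 days after it.

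**5. Scale, as an illustration only.** Power of the two-stage rule (at least 1 of 16, then at least 2 of 29) is 1 - (1-p)^16 - 16p(1-p)^28. At p = 0.15 this is 1 - 0.0743 - 0.0254 = 0.9004, which reproduces the stated 90.04%. Suppose, pessimistically, that k of 29 subjects are measured off drug and respond at the 1% null rate, and use the averaged rate:

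- k = 1: p = (28 × 0.15 + 1 × 0.01)/29 = 0.1452, power about 89.0%.
- k = 5: p = (24 × 0.15 + 5 × 0.01)/29 = 0.1259, power about 83.7%.

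The protocol supports neither value of k nor a complete loss of response, so these figures only show how the design reacts and are not estimates.

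**The case against.** The text already contains the binding limit and its reason, so a careful site would follow it and treat the table heading as a slip. The excess is one day, with one drug-free day before the visit. Tablets left over from missed doses could extend dosing. Any bias works against the drug and would not create a false claim of benefit. All of this stands, and it keeps the point small. It does not remove the contradiction, because the protocol does not say whether the table or the text governs.

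On Section 15 the objection is stronger. The bullet is a general retention step, worded as an attempt, and its interval may describe the staff's effort to make contact and rebook instead of the new visit date. A visit-specific limit with a stated reason would naturally prevail over it, and the bullet itself points participants back to the schedule. A reader might infer that the protocol requires an off-drug measurement whenever the Day 28 visit is missed. That does not follow: it needs the 2 days to be read as a minimum and the Day 29 limit to be ignored. What remains is that the bullet is silent on windows and can be read to allow Day 30 to 33.

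Handling of out-of-window values can be left to the SAP. The SAP cannot, however, recover an on-drug FEV1 that was never taken, so the booking window has to be right in the protocol.

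**Conclusion.** The point holds as an internal contradiction about the primary-endpoint visit. The table permits Day 30; the text stops at Day 29 because of drug supply. With dosing from Day 1 and no missed doses, a Day 30 FEV1 is taken two days after the last dose and is not a measurement during week 4 of treatment. The loose wording in Section 15 is secondary, and whether it conflicts depends on how it is read.

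A reader might also infer that the week-4 response rate will be biased by a known or material amount. The documents do not support that. They give no time course for loss of FEV1 after stopping, no expected number of late visits and no missed-visit rate. Only the direction can be stated: any bias would tend to miss a responder.

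**What to change.** 1. In the Section 6 schedule table, change the Study Visit 4 window from plus or minus 2 to +1/-2, in both places where the heading appears.
2. In the missed-visit bullet of Section 15, add a clause such as: *rebooking stays within the visit window where possible, and the Day 28 visit takes place no later than Day 29.*

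The cost is one column heading and one clause, with slightly less scheduling flexibility for the site. Design, sample size and analysis do not change. Reporting of a visit that is late all the same is already covered by the protocol-deviation process in Section 20.

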### **16. Risk to Participants**

#### **Blood Draws**

Possible risks include hematoma at the needle site and minimal pain due to the venous puncture procedure.

#### **Sweat chloride testing**

The Macroduct system is used in hospitals and clinics worldwide to perform sweat chloride testing. This is considered a very safe, painless procedure, but rare minor burns have been reported at the electrode site (although participants may show no discomfort during the test). To further minimize risk, all equipment will be properly cleaned and evaluated before and after the procedure by personnel trained in performance of this assay.

#### **Risks of the punch biopsy**

Significant pain, bleeding, or infection are very rare with this type of punch biopsy. Investigators may use a topical anesthetic on the skin in order to minimize pain, although study subjects might feel minor discomfort (like a scratch) when the topical anesthetic is administered, and the next day. There is the possibility of a very small scar.

#### **Risks from Study Drug (Trikafta™ (elexacaftor 100 mg/tezacaftor 50 mg/ivacaftor 75 mg (2 pills once daily in the morning) and ivacaftor (150 mg) once daily in the evening)**

There may be side effects from the Study Drug or procedures that are not known at this time. Examples of adverse reactions known in patients receiving Trikafta™ are listed below.

**Protocol Title: Evaluating Trikafta for the treatment of patients with non-cystic fibrosis bronchiectasis (NCFBE)**

The most common (occurring 5% or more) risks and discomforts expected in this study are:

|                                            |     |
|--------------------------------------------|-----|
| Headache                                   | 17% |
| Upper respiratory tract infection          | 16% |
| Abdominal pain                             | 14% |
| Diarrhea                                   | 13% |
| Rash                                       | 10% |
| ALT increased (a liver enzyme)             | 10% |
| Nasal congestion                           | 9%  |
| Blood CPK increased (a muscle enzyme)      | 9%  |
| Rhinorrhea (runny nose)                    | 8%  |
| Rhinitis (nose irritation)                 | 7%  |
| AST increased (a liver enzyme)             | 9%  |
| Influenza                                  | 7%  |
| Sinusitis                                  | 5%  |
| Blood bilirubin increased (a liver enzyme) | 5%  |

Increased liver enzymes (ALT or AST) in the blood have been observed in some subjects. Very high levels of these enzymes could lead to stopping of Study Drug. The abnormal blood tests may improve after Study Drug is stopped. In some severe cases, high liver enzymes can become permanent or even life-threatening.

Possible Risks Based on Animal Studies

In a study in which ivacaftor (a component of Trikafta™) was given to newborn rats, cataracts (cloudiness of the lens of the eye) were seen. No cataracts were seen in studies of older animals (rats and dogs) dosed with ivacaftor for longer periods of time. The importance of this finding in humans is unknown.

Drug Interaction Risks

The combination of the Study Drug and other medications, dietary supplements, natural remedies, and vitamins could be harmful to trial participants. Subjects will be asked to inform study staff about every medicine, dietary supplement, natural remedy, and vitamin (or change in medicine) while they are in the study. The study staff will review all medications (including herbal medications, such as St. John's Wort, grapefruit or grapefruit juice) that should not be utilized during the study because herbal compounds such as these can alter metabolism of Trikafta™.

Risks of Discontinuing Study Medication:

Once the four-week treatment period is complete, participants will no longer receive Trikafta™. There is a chance that the NCFBE will improve when taking Trikafta™. However, NCFBE symptoms may appear to worsen after the participant stops taking Trikafta™ as respiratory function returns to baseline.

Women:

**Protocol Title: Evaluating Trikafta for the treatment of patients with non-cystic fibrosis bronchiectasis (NCFBE)**

---

To protect against possible side effects of the Study Drug, women who are pregnant or nursing a child may not take part in this study. If a participant becomes pregnant, there may be risks to the participant, the embryo, or fetus. These risks are not yet known. If the participant is a woman of childbearing ability, the participant and the Study Doctor must agree on a method of birth control to use throughout the study. Pregnant women will be taken out of the study.

Possible risks to non-study participants:

The effect of the Study Drug on sperm is not known. To protect against possible side effects, if the female partner of a male participant becomes pregnant during the Study, they should notify the Study Doctor right away. If a male participant's female partner becomes pregnant, he will need to stop Study Drug immediately.

Study Drug should be kept out of the reach of children or anyone else who may not be able to read or understand the label. Participants should not allow anyone else take the Study Drug.

It is possible that new information regarding Study Drug or participation in the trial during the course of the clinical protocol will become evident. If this happens, patients will be informed so that they can make a decision about continuing in the study (see also Section 9). Participants in the trial may be asked to sign a new consent form that includes the new information in order to continue in the study.

**17. Potential Benefits to Participants**

This study is not designed to benefit the participant directly. NCFBE may improve in this study but it may not, and it may also become worse. This study will provide new information regarding whether cells from the skin can be used to predict patients with NCFBE who respond best to new drug therapies.

